| 
Among children receiving active treatment versus placebo:
 
(1) Is there a difference in the (a) duration of vomiting, (b) frequency of vomiting, or (c) the proportion who experience vomiting following ED disposition.
 
(2) Is there a difference in the proportion who require an unscheduled health care provider visit?
 
(3) Is there a difference in the proportion who require intravenous rehydration?
 
(4) Is there a difference in the satisfaction with care?
 | 
1. Vomiting: Frequency, Duration, Proportion
 
2. Health Care Use: ED, Primary Care
 
3. Intravenous rehydration
 
4. Caregiver Satisfaction with Therapy Provided: Likert Scale
                                                                              |                                                                                                                        |
| Safety                                                                                                                                                                                                                                                                                                                                                                                                                                                                                                  |                                                                                                                                                                                                                                                                                     |                                                                                                                        |

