## 6.3 MEASURES TO MINIMIZE BIAS: RANDOMIZATION AND BLINDING

**Sequence Generation:** A biostatistician will generate a randomization list stratified by site and weight, which will then be uploaded to an internet based randomization service that uses random-number generating software. The lists will be sent to the central research pharmacy located in Calgary, Alberta who will disseminate the lists to the appropriate site research pharmacies. Kits will be prepared and labelled on site at each participating institutional research pharmacy. The kits will be stored in the local site research pharmacies until dispensed to the ED for recruitment needs.

**Allocation Concealment:** Randomize.net uses industry standard security to send data over the internet. Randomization will be blocked using random blocks of 4 and 6 with a 1:1 allocation ratio. Stratifying by clinical site and weight and blocked randomization will ensure that variations (e.g. site specific practice patterns, gastrointestinal pathogens) are comparably distributed across treatment arms. Only the research pharmacy at the coordinating centre and www.randomize.net will retain the randomization code.

**Implementation:** Potentially eligible patients will be screened. A log of all screened patients will be maintained. If eligible, the details of the study will be discussed with the caregivers and potential patients. If consent is obtained, enrolled participants will be assigned a participant ID number by the clinical site via REDCap (i.e record ID). Baseline demographic clinical variables will be collected and the data collection forms will be completed either on paper or directly into the secure online REDCap database via electronic tablet. The research team member will

then log into randomize.net which will randomize the patient (i.e. it will provide a kit number that corresponds to a study drug kit at the clinical site which will be given to the patient).

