## 8 STUDY ASSESSMENTS AND PROCEDURES

### 8.1 EFFICACY ASSESSMENTS

Primary and secondary endpoints will be determined by the outcome measures. Assessments performed will support the outcome measures listed in Section 3.0 Objectives and Endpoints.

**Screening:** Participants presenting to the ED of a participating institution will be screened for eligibility using the eligibility criteria listed in sections 5.1 and 5.2 by a trained research team member. The research team member will ask the caregiver questions related to the patient's medical history and current medications that may be contraindicated. Inclusion/exclusion criteria will be determined based on caregiver report of patient's medical history and the details of their current illness. This information will be confirmed with the treating physician to ensure accuracy of reported information and medical oversight. In addition to the patient's medical history, eligibility depends on the treating physician ordering at least 1 dose of ondansetron while the patient is still in the ED, as well as the patient's ED diagnosis. This information will be confirmed using physician or nursing orders and the patient's ED medical chart by the research team member. Permission to access the patient's chart for screening purposes will be obtained from the caregiver/legally authorized individual, in accordance with provincial access to health information legislation.

**Enrollment/Baseline Assessments (outcome assessment):** A baseline questionnaire will be performed to obtain information supporting the study's outcome measures (e.g. *current medical history, duration and frequency of vomiting, presence of fever, duration and frequency of diarrhea, satisfaction scale, etc.*).

In addition to the questionnaire listed above, the trained research team member will obtain the participant's heart rate (HR) and respiratory rate (RR) at the Enrollment/Baseline visit. The triage temperature and weight will be obtained from the ED medical record. To obtain a baseline understanding of the participant's health and medical condition, a basic review of systems and concomitant medications will also be performed.

**Follow-up:** Outcome measure end-point data will be obtained using follow-up questionnaires performed 24, 48, and 168 hours (7 days) after the Baseline/Enrollment visit Time 0 (Consent date and time) by research study staff. Questions will be asked related to the following:

- Frequency and duration of vomiting

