- Frequency and duration of diarrhea
- Presence of fever
- Return to healthcare provider (resource utilization)
- IV rehydration
- Satisfaction with care and medications provided

**Chart Review:** The study consent form will contain details regarding the review of medical charts for study purposes. At the baseline/enrollment visit, the ED medical record will be reviewed to collect data points outlined on the Enrollment CRF including, but not limited to; triage date/time, ED disposition, discharge date/time, triage weight, triage temperature, and medications administered during the ED enrollment visit.

A review of the participant's medical chart will also take place between 8 – 30 days after the 168 hour time-point to collect data related to revisits to a health care provider that occurred within 7 days of enrollment for the current illness as defined in Section 3.0. Information regarding type of revisit, treatment provided, discharge diagnoses, and disposition will be collected.

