6. **Unscheduled healthcare visit:** Presence of an unscheduled healthcare visit will be collected on the questionnaire and will be classified as “none”, “primary care”, or “emergency department”. All revisits to the participating site are verified by database review.
7. **Treatment:** Treatment will be classified as “none”, “intravenous rehydration”, or “hospital admission”. If the participant is admitted directly following their enrollment ED visit and that admission stay is longer than 48 hours, it will be counted as treatment in the post enrollment MVS. If the participant’s enrollment admission stay was less than 48 hours, it will not be counted as “treatment”.

Data needed to calculate the MVS will be collected at Enrollment (Day 0), on the 24, 48, and 168 hour questionnaires, and verified using chart review performed within 37 days of participant enrollment. The primary outcome will be tabulated by treatment for each site and weight stratum. A Mantel-Haenszel statistic, assessing the effect of treatment on the primary outcome controlling for strata, will be calculated to test the primary hypothesis. Summary statistics for the effect sizes will be given. Choice of final summary statistic reported (e.g. risk difference, risk ratio, or odds ratio) will be based, in part, by which statistic is least variable across subgroups (i.e. shows the smallest degree of interaction across subgroups). It is expected that the asymptotic version of the Mantel-Haenszel test will be appropriate for the final analysis. In the case of low outcome counts, the Mantel-Fleiss criterion will be assessed. If the criterion has a value less than 5, the exact version of the Mantel-Haenszel test will be used and the two-sided p-value will be defined as the sum of all probabilities of test statistics with point probabilities less than or equal to that of the observed value. In the event any patients were randomized within an incorrect stratum due to misspecification at time of randomization, the actual, rather than assigned category will be used in the above analysis.

Although randomization should result in approximate balance between treatment arms with respect to critical baseline variables affecting the outcomes, additional exploratory analyses will be conducted to assess the effects of treatment after adjusting for baseline covariates in models for the primary outcome.

The covariates considered are:

- Baseline MVS (actual score)

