5. **Proportion of participants who require intravenous rehydration:** If the participant required an unscheduled health care visit (see #4 above), the participant will be asked additional questions related to intravenous (IV) insertion, treatment course, and disposition. Intravenous fluids administered at the index visit will not be included as part of this outcome.
6. **Caregiver satisfaction as measured by a 5-point Likert scale in the 48 hours following ED disposition:** Caregiver satisfaction with the therapy provided (oral ondansetron or placebo) in the 48 hours following ED disposition. This will be measured using a 5 point Likert scale on the questionnaire administered 168 hours after Time 0.

The analysis of secondary outcomes will be undertaken as detailed below:

1. **Frequency of vomiting from study enrollment to Day 7:** The total number of episodes of vomiting and diarrhea related to the presenting illness will be compared between groups (active and placebo) using a generalized linear model to compare differences between Poisson rates whilst adjusting for stratification.

2. **Duration of vomiting :** The total number of days the participant experiences vomiting from Day 0 to Day 7 will be compared using the Van Elteren test, stratified by center and duration of symptoms (pre-enrollment). If a number of patients still experience symptoms at the 7-day follow-up questionnaire, this will be tested using a suitable procedure to take account of censoring such as median regression or additive hazard models. Additional analyses involving this outcome will include linear regression models that adjust for possible effects of baseline characteristics.
3. **Proportion of participants who experience vomiting within 7 days of enrollment:** The proportion of participants with vomiting following enrollment will be compared using Mantel-Haenszel test stratified by site and weight.
4. **Proportion of participants who require an unscheduled health care provider visit within 7 days of enrollment:** The proportion of participants who require an unscheduled health care provider visit within 7 days of enrollment will be compared using Mantel-Haenszel test stratified by site and weight.

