5. **Proportion of participants who receive intravenous rehydration:** The proportion of participants who receive intravenous rehydration will be compared using Mantel-Haenszel test stratified by site and weight. If the number of participants requiring intravenous rehydration is low then exact calculations without stratification may be required.
6. **Caregiver satisfaction as measured by a 5-point Likert scale in the 48 hours following ED disposition:** Caregiver satisfaction with the therapy provided (oral ondansetron or placebo) in the 48 hours following ED disposition will be compared using a Mann-Whitney U Test.

---

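### The satisfaction endpoint is tested without the satisfaction rating already taken at baseline; the test is valid but may give up some precision

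*Combined protocol and SAP*

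**What the plan says.** - **Baseline.** Section 8.1 describes a baseline questionnaire meant to support the outcome measures. Its examples include "duration and frequency of diarrhea, satisfaction scale". The documents do not say what that scale rates, how many points it has, or whether it matches the later item.
- **Timing.** Section 6.3 (Implementation) says "Baseline demographic clinical variables will be collected" and only then has the team member log in to the randomisation service. It does not name the satisfaction item; I take the baseline questionnaire to be part of this step.
- **Endpoint.** Sections 3 and 9.4.3 define it as caregiver satisfaction with the therapy provided, ondansetron or placebo. On timing, Section 9.4.3 says: "This will be measured using a 5 point Likert scale on the questionnaire administered 168 hours after Time 0".
- **Analysis.** Under Section 9.4.3, analysis item 6, satisfaction "in the 48 hours following ED disposition will be compared using a Mann-Whitney U Test". No covariate or stratum is mentioned.
- **Multiplicity.** Section 9.4.1 places satisfaction in a Holm procedure over eight secondary tests.
- **Covariates elsewhere.** Section 9.4.2 plans exploratory analyses "adjusting for baseline covariates in models for the primary outcome". Baseline satisfaction is not in that list.
- **Looser wording.** Objective 4 in Table 1.0 asks: "Is there a difference in the satisfaction with care". The follow-up topics in Section 8.1 include "Satisfaction with care and medications provided".

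**The concern.** A rating gathered before allocation to support an outcome is a natural covariate for that outcome, yet no analysis in Section 9.4 uses it. Caregivers differ in how generously they rate anything, and some of that difference should already show at baseline. Section 6.4 also lets a caregiver give no doses and remain compliant, so some 168-hour ratings may reflect general disposition more than the study drug. Variation of this kind is unrelated to arm and widens the comparison.

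The omission also stands out within Section 9.4.3. The other five secondary analyses all account for stratification or centre: a stratification-adjusted Poisson model, a Van Elteren test and three stratified Mantel-Haenszel tests. Vomiting duration also gets regression on baseline characteristics. Satisfaction gets none of this. What is at stake is some power on one Holm-tested secondary endpoint, not the validity of its result.

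**Working it through.** **1. The plan's own figure.** No power or sample size is stated for satisfaction. The primary calculation in Section 9.2 (30% vs 20%, two-sided 0.05, 90% power, 1:1) does reproduce:

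n per arm = [1.960·√(2·0.25·0.75) + 1.282·√(0.30·0.70 + 0.20·0.80)]² / 0.10² = 392, so 784 in total, as stated.

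Inflation: 784/0.90 = 871 (stated 870); 870/0.92² = 1028 (stated 1030). Both agree apart from rounding.

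**2. Number analysable for satisfaction.** 1030 × 0.90 = 927, or about 463 per arm.

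**3. Normal approximation.** Let ρ be the correlation between the baseline and 168-hour ratings (assumed). Adjustment multiplies the residual variance by 1 − ρ², a cut of 4% at ρ = 0.2, 9% at 0.3 and 25% at 0.5. Take an effect for which the unadjusted comparison has 80% power:

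- at two-sided 0.05: d = √(2/463) × (1.960 + 0.842) = 0.184 SD
- at the first Holm step, 0.05/8 = 0.00625: d = √(2/463) × (2.734 + 0.842) = 0.235 SD

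Adjusted power = Φ( d / √(2(1 − ρ²)/463) − z ), with z = 1.960 or 2.734.

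| ρ | power at 0.05 | power at 0.00625 |
|---|---|---|
| 0 | 80.0% | 80.0% |
| 0.1 | 80.4% | 80.5% |
| 0.2 | 81.6% | 82.0% |
| 0.3 | 83.6% | 84.5% |
| 0.5 | 89.9% | 91.8% |
| 0.7 | 97.5% | 98.8% |

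**4. Simulation on a 5-point scale.** Assumptions: response shares 3/5/12/30/50% from lowest to highest, a latent shift of 0.2 SD, 463 per arm, 4,000 runs per setting. The Mann-Whitney test is set against a regression of the outcome ranks on arm and baseline ranks (rank ANCOVA).

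| ρ | at 0.05: Mann-Whitney → rank ANCOVA | at 0.00625: Mann-Whitney → rank ANCOVA |
|---|---|---|
| 0 | 74.9% → 75.0% | 46.0% → 46.4% |
| 0.2 | 74.8% → 75.9% | 46.4% → 48.3% |
| 0.3 | 74.7% → 77.7% | 45.5% → 49.0% |
| 0.5 | 74.6% → 81.1% | 45.1% → 55.5% |
| 0.7 | 75.1% → 90.2% | 44.6% → 69.5% |

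With no shift, both tests rejected between 4.5% and 5.3% of the time at 0.05.

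**5. Reading the two together, at 0.05.** The gain is about 0 to 2 points for ρ from 0 to 0.2. At ρ = 0.3 it is 3.0 (77.7 − 74.7) to 3.6 (83.6 − 80.0). At ρ = 0.5 it is 6.5 (81.1 − 74.6) to 9.9 (89.9 − 80.0). At the first Holm step the gains are slightly larger: 3.5 to 4.5 points at 0.3 and 10.4 to 11.8 at 0.5.

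**The case against.** The strongest reply is that the baseline item is not a baseline value of the endpoint. The endpoint rates home therapy that has not yet been given, and the plan describes the baseline item in two words within a list of examples. It may rate something else, on another scale, about a week before the outcome is asked. A correlation of 0 to 0.2 is then plausible and the gain negligible. An unadjusted rank test for one Likert outcome is also a conventional choice, and no power target is set for it. All of this stands. It limits the size of the point, but does not explain why a rating collected to support the outcomes has no planned use.

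A reader might infer more in three ways, none of which the documents support.

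- **That power is definitely lost.** This needs a correlation above zero, and the documents give none.
- **That index ED care biases the comparison.** That care precedes allocation, so randomisation balances it in expectation. It can add noise but not bias, and the simulated type I error is held.
- **That the endpoint must be redefined as a medication-only item.** Sections 3 and 9.4.3, and the endpoint cell beside objective 4 in Table 1.0, already define it as satisfaction with the therapy provided. The Section 8.1 follow-up entry is a list of question topics and may cover two separate items. Only the wording is loose.

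**Conclusion.** The point holds as a minor efficiency matter. A satisfaction rating is listed at baseline, and the planned Mann-Whitney comparison uses neither it nor the strata. The planned test is valid. The possible gain in power at two-sided 0.05 runs from nothing, if the two ratings are unrelated, to about 6 to 10 points at a correlation of 0.5. This rests on about 463 analysable per arm, an assumed correlation, assumed effect sizes and, in the simulation, assumed response shares. It also assumes that the satisfaction item is completed before the kit is assigned, as the order of steps in Section 6.3 suggests. The primary analysis is not touched.

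**What to change.** In Section 9.4.3, analysis item 6, pre-specify before unblinding a rank analysis of covariance of the 168-hour rating that includes the baseline satisfaction rating, and keep the Mann-Whitney test as a sensitivity analysis. State there what the baseline item rates, and give a rule for missing baseline ratings that does not depend on arm. Adding site and weight would match most of the other secondary analyses, but is optional and is not covered by the figures above. Align the mentions of care in Table 1.0 (objective 4) and in the Section 8.1 follow-up list with the existing therapy definition.

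The cost is SAP wording, one covariate already collected and the missing-data rule. The rank version adds no distributional assumption for the outcome; a proportional-odds model would add one. If the baseline item proves unrelated to the endpoint, the change brings little or no gain. Fixing the choice in advance also removes any later choice between adjusted and unadjusted results.

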## 8.2 SAFETY AND OTHER ASSESSMENTS

The following assessments will be performed to ensure the safety of patients as they participate in the study and to assess safety endpoints as described below:

- Frequency and maximal number of diarrheal episodes during the 48 hours following randomization
- Palpitations
- Syncope
- Chest pain

- Arrhythmias
- Serious Adverse Events

Please reference Section 1.3 SoA for a list of all study events/visits.

If caregivers report any symptoms of concern to the research team (palpitations, arrhythmias, syncope, etc.) or are concerned about their child's health, they will be advised to follow up with their health care provider or seek immediate medical attention at the nearest hospital. Caregivers will be provided with a list of possible reasons to seek medical care and a disclaimer regarding symptoms of concern and the required action will be included on all follow-up questionnaires.

**Screening:** A detailed review of the patient's medical history related to the eligibility criteria (e.g. history of prolonged QT syndrome, currently taking apo morphine, etc.) will be performed by the qualified research team member with the caregiver. The information will then be confirmed by the treating physician to comply with medical oversight and ensure patient safety. We will rely on caregiver report of current medications and the medical history of the patient to assess eligibility.

**Baseline/Enrollment Visit – Review of Systems:** After the patient is deemed eligible and has consented to participate in the study, a review of systems will be performed by the qualified research team member to obtain baseline health information prior to starting the study intervention. The research team member will ask the caregiver/participant questions related to the participant's general health by system (e.g. cardiovascular, respiratory, musculoskeletal, etc.). This allows the research team to more accurately measure any new symptoms or conditions that occur after enrollment in the study. During the review of systems, the research team will also ask the caregiver/participant if they are currently taking any medications or supplements. This information will be recorded on study case report forms. This process will take place after the clinical dose of ondansetron is administered however it must be completed prior to the participant taking the first dose of study medication.

**Baseline/Enrollment Visit – Vital Signs:** The qualified research team member will obtain the following vitals from the participant prior to study medication administration and/or discharge from the ED (whichever arrives first): Respiratory Rate (RR), Heart Rate (HR), temperature, and weight at triage. All measurements will be obtained from the medical chart however if considered unreliable or if the values are unavailable, research staff will obtain these measurements while the patient is still present in the ED. The procedure for collection of vital signs will be outlined in the TMOP and site specific SOPs.

**Hour 24, 48, and 168 Follow-up – Study Intervention Adherence and Administration of Questionnaires:** A follow-up questionnaire will be provided to the caregiver via email or telephone (based on their indicated preference). Each questionnaire will ask if the caregiver administered any doses of the study intervention and if administered, will prompt for the most recent date/time of administration. Questionnaires will also provide prompts for feedback regarding the child's illness/condition which will prompt additional questioning related to possible adverse events.

**Hour 24, 48 and 168 Follow-up – Assessment of Adverse Events:** Obtained from the follow up questionnaire/telephone call completed by trained research staff. Adverse events will be followed until such time as they resolve or are classified as non-progressive to a maximum of 1 month after the start date of the event or until it is apparent that the event will not resolve completely. Trained research staff will follow up with caregivers on a regular basis (daily or weekly, depending on the event details).

Any results obtained from the assessments listed above will not be communicated with the participant or their caregiver unless deemed clinically significant by the site investigator (e.g. Adverse Events reported by the caregiver, abnormal heart rate, etc.).

